## Study participants

Study participants will consist of three groups selected from residents of the health center catchment areas randomized to the control or intervention arms and will be selected as follows:

1. Individuals in households selected for endline sampling. Households will be identified as describe in section 2.5 (page 23)
2. Individuals living within 140 meters of an index case selected for a CHW-led reactive response (Figure 6)
3. Individuals living within 140 meters of an index case selected for a research team supported reactive response (see Section 2.4.1 and Figure 7), who will receive additional follow-up visits 3, 30 and 90 days after the initial reactive response.

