### Directly Observed Treatment (DOT)

DOT describes a system whereby patients taking a treatment dose are directly observed throughout the treatment course, thereby ensuring maximal compliance with the drug regime. In the context of malaria elimination, compliance is important for preventing the development of drug resistance and also fully removing the infectious reservoir from the population. To fully exploit the window of chemoprophylaxis, i.e. the period where drug levels protect treated individuals from being infected by an infectious mosquito bite, the entire target population needs to comply with the treatment regime. Therefore, a modified DOT schedule will be implemented wherein treatment is directly observed on day 1 and day 3, but not on day 2 for all individuals within a reactive response in the intervention and control arms. Treatment blister packs will be observed on Day 3 as a proxy of compliance for Day 2.

As stated in Section 2.2.2.1 on p17, DHAP needs to be taken on an empty stomach, and in certain cases this may prevent DOT being implemented.

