Table 4 - Summary of inclusion / exclusion criteria and consent/assent forms. * RFTAT with AL represents current standard of care so consent / assent will not be required.

The development of drug resistance has been linked to the administration of therapeutic doses of antimalarials

^11^. Our proposed strategy to reduce the risk of the development of drug resistance includes:

- Directly observed treatment of the first dose of DHAP during all reactive responses
- In research responses, the team will additionally:
  - Check blister packs on day 3 to ensure that the second dose was taken
  - Directly observed treatment of the third dose of DHAP on day 3

Our proposed strategy to reduce risks associated with finger sticks includes:

- To clearly explain the procedures to each individual or caretaker so that they understand the transient pain associated with collection of finger prick blood samples and the extremely low risk of infection.
- To use specially trained and supervised fieldworkers who will be able to answer commonly asked questions.
- To specially train fieldworkers to collect and handle biological specimens and ensure that all data entry personnel are trained on confidentiality and safety issues, as well as on informed consent procedures. This includes special training for all team members on universal precautions for handling biological specimens.

DHAP has been approved by the Zambian Ministry of Health as the new alternate first-line standard of care drug for the treatment of uncomplicated malaria in Zambia. AL is also the first-line treatment for uncomplicated malaria and is widely available. A new Cochrane Review (2014) has shown that studies comparing DHAP to other antimalarials to be safe, effective and well-tolerated by individuals

^47^. DHAP is a combination of two antimalarial drugs (dihydroartemesinin and piperaquine). Dihydroartemesinin has been associated with the following: prolonged QT intervals, falciparum malaria, influenza, cough, fever, abnormal cardiac conduction, necrotizing enterocolitis in foetus or new-borns, leukocytosis, neutropenia, thrombocytopenia, hepatitis and seizure. The risk of DHAP is assumed similar to that of AL, the current widely available national first line treatment for uncomplicated malaria.

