Adverse reactions to both RFTAT with AL and RFDA with DHAP will be assessed 3 days following the reactive responses when the CHW or research team checks for drug compliance. Percentage of administrations causing adverse reactions will be calculated as the number of adverse reactions detected divided by the number of administrations in the health center catchment. Risk factors for adverse reactions such as age and sex will be examined as needed. The key to managing side effects and potential adverse events (AEs) and serious AEs (SAEs) is through thorough training of CHWs, health facility staff and supervisors, and intensive sensitization of the community. CHWs will monitor their respective communities for AEs and refer any potential SAEs to designated health facilities. Health workers at these facilities will be informed of the program, potential side effects, and provided with AE reporting forms (Appendix 13). Cases that cannot be treated at health centers will be referred to nearest district referral centre or district hospitals, with transport provided by the study.

Any and all potential AEs following treatment with DHAP will be recorded through passive case detection at all local public and private health facilities in the target areas, including referral by CHWs. A data safety monitoring board (DSMB) will be established to oversee and report on any AE and SAEs that are potentially linked to the administration of DHAP, and as outlined in further detail in Section 3.2. The following steps will be taken for all SAEs that present to health facilities:

1. The health facility will complete an AE description form (Appendix 13). The completed form will then be submitted to the DSMB, study coordinator and principal investigator within 72 hours from the identification of the AE/SEA.
2. The DSMB will complete an AE investigation form (Appendix 14) to a) assess if the event is an SEA, and 2) to determine if the AE/SEA was caused by the administration of DHAP as part of this study within 24 hours.
3. The DSMB will provide the completed AE investigation form to the PI, who will submit to the Research Ethics Committees (RECs) at UNZA and PATH. The respective RECs will be notified within 24 hours of the DSMBs completion of the AE investigation form for events determined to be SEAs, and within 48 hours of DSMB notification if deemed an AE, but not an SEA.

Our proposed strategy to reduce risks associated with DHAP in pregnancy (first trimester) include:

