## Data and safety monitoring plan

An independent data safety monitoring board (DSMB) will be established consisting of at least 5 independent experts in malaria control, diagnosis, case management, biostatistics and epidemiology and one member of the research team who will receive monthly reports of adverse events during the intervention period of the trial. The charter will include trial stopping rules for safety. No data on futility or benefit will be determinable during the course of the trial as seasonality of malaria transmission timing of outcome data collection preclude developing stopping rules based on outcome data collected during the duration of the implementation of the intervention. Safety concerns associated with the wide scale use of DHAP, although unexpected, will form the basis of development of a stopping rule. The stopping rules for this trial will be based on detection of a significantly higher rate of mortality, hospitalization for possible drug related events, or any other severe adverse event in the RFDA intervention arm compared to expected rates in the control group.

In addition to the DSMB, a regional monitor will be used for supervision of study progress and adverse events. A study pharmacist from the provincial health office will also be used to manage and account for the supply of DHAP used in the study.

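### The adverse-reaction percentage uses all administrations as its denominator while the protocol contradicts itself on who is checked at day 3, and a comparable control-arm rate for the stopping rule is not clearly secured

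*Protocol*

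**What the plan says.** **The rate.** Section 3.1 (Adequacy of protection against risks) states: "Adverse reactions to both RFTAT with AL and RFDA with DHAP will be assessed 3 days following the reactive responses". Either the CHW or the research team may make this assessment, as part of the compliance check. The percentage is then the "number of adverse reactions detected divided by the number of administrations in the health center catchment".

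**Day-3 contact, broad wording.** Section 2.4.2 (Directly Observed Treatment) says "treatment is directly observed on day 1 and day 3, but not on day 2 for all individuals within a reactive response", and applies this to both arms. Secondary Aim 3 lists a day-3 visit to assess adverse reactions among the procedures of the cluster randomised trial.

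**Day-3 contact, narrow wording.** Section 2.3 (Study participants) names three groups. Only the research-response group is described as people "who will receive additional follow-up visits 3, 30 and 90 days after the initial reactive response". The drug-resistance list in Section 3.1 promises observation of the first dose in all responses. It places the day-3 blister-pack check and observation of the third dose under the line "In research responses, the team will additionally". Table 2 (Section 2.7, Consent) shows the 3-day follow-up only beneath the reactive research response. Appendix 9, the 3-day questionnaire, is labelled as being for research responses.

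**Facility events.** Section 3.1 says: "Any and all potential AEs following treatment with DHAP will be recorded through passive case detection at all local public and private health facilities". It sets the monitoring board's task as overseeing events potentially linked to DHAP. It then applies the reporting-form steps to every serious event that presents to a facility, and it has CHWs watch their communities for adverse events without naming an arm.

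**Stopping.** Section 3.2 (Data and safety monitoring plan) bases stopping on a significantly higher rate of mortality, hospitalisation for possibly drug-related events, or "any other severe adverse event in the RFDA intervention arm compared to expected rates in the control group". The rules themselves are to be in the board's charter.

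**The concern.** There are three related faults.

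1. A reaction can be detected at a day-3 check only where that check takes place. If the denominator includes administrations that were never checked, each one is counted as reaction-free and the reported percentage is too low. Whether this happens depends on a question that the protocol answers in two ways.
2. The stopping rule refers to the control group, but the sentence on facility recording and the board's remit refer to DHAP. The board could be left comparing RFDA events with a benchmark that is neither defined nor clearly collected in the same way. A real excess could then be missed, or ordinary background illness taken for drug harm.
3. A rate per administration does not describe the same kind of person in each arm. AL is given to RDT-positives and DHAP to everyone within 140 metres.

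The stakes are real. Section 3 says that focal drug administration has not yet been used for malaria control in Zambia, most DHAP recipients would test negative if tested, and safety is the only ground for stopping that Section 3.2 allows.

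**Working it through.** The protocol states no expected adverse-event rate, safety threshold or safety power, so there is no figure of its own to reproduce. The arithmetic below only shows how large the problem could be.

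**Inputs**
- People in reactive responses: about 30,000 (Project summary, Sample size).
- Re-infection / importation / serology subset: about 9,000 (same place), taken here as the research-response participants.
- RFTAT positivity: Table 1, 20 proposed sites, range 5.2% to 19.2%, median 8.3%, unweighted mean 9.0%.
- Assumptions: participants stand in for administrations; an administration is a course; the 30,000 split equally, 15,000 per arm; reactions enter the numerator only through day-3 checks.

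**Step 1: dilution of the percentage.** Let *c* be the share of administrations with a completed day-3 check.

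Reported percentage = true percentage × *c*.

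- Broad wording, all checked: *c* = 1.
- Narrow wording, research responses only: *c* = 9,000 / 30,000 = 0.30, an understatement of 30,000 / 9,000 = 3.3-fold.

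| True percentage | *c* = 1 | *c* = 0.75 | *c* = 0.5 | *c* = 0.30 |
|---|---|---|---|---|
| 1% | 1% | 0.75% | 0.5% | 0.3% |
| 5% | 5% | 3.75% | 2.5% | 1.5% |
| 10% | 10% | 7.5% | 5% | 3% |

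The middle columns also cover the case where every response is due a visit but some visits are missed. Missed visits count as reaction-free on either wording.

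**Step 2: effect on a comparison of arms.** The reported ratio equals the true ratio × *c*(RFDA) / *c*(RFTAT). With equal coverage the factor is 1 and the ratio is unbiased. With assumed coverage of 30% in RFDA and 50% in RFTAT, equal true rates give 0.30 / 0.50 = 0.6.

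**Step 3: who is in each denominator.** AL courses per arm = 15,000 × positivity:
- 15,000 × 0.052 = 780
- 15,000 × 0.090 = 1,350
- 15,000 × 0.192 = 2,880

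DHAP courses are at most about 15,000, before exclusions and refusals. At the median positivity there is one AL course per 1 / 0.083 = 12 people tested, against about one DHAP course per person. The AL denominator is confined to RDT-positives, while the DHAP denominator is mostly people who would test negative.

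**Step 4: safety channels set against the stopping rule.**
- Day-3 reactions: both arms, but coverage is contradictory, and Section 3.2 does not use this percentage for stopping.
- CHW community monitoring: no arm named.
- Facility recording of adverse events: worded for DHAP.
- Form steps for serious events: worded for all of them. However, the sentence follows directly on the DHAP-worded remit, and the board's causality question in step 2 of that list concerns DHAP only.
- Comparator in the stopping rule: expected control-group rates, with no source and no statement of whether they are observed or assumed.

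A serious event in a control catchment therefore probably reaches a form, but no stated route turns it into an arm-level rate.

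**The case against.** A reader might infer that there is no control-arm safety rate at all, that deaths and hospital stays are captured only for people given DHAP, and that the stopping rule therefore cannot work. The protocol does not support this. Day-3 reactions are assessed in both arms, CHW monitoring names no arm, and the form steps cover every serious event at a facility. The expected control rates could be background figures defined in the charter, which is not available here. Nor is the day-3 percentage named as a stopping metric, so the 3.3-fold figure says nothing about when the trial would stop.

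Other points against the concern:
- The paragraph that defines the rate has the CHW or the research team make the check, so read alone its numerator and denominator match.
- The 3.3-fold figure is a worst case. The numerator is reactions detected, and some could come to light through CHWs or facilities.
- The 30,000 and 9,000 are people. In the control arm only a fraction are treated, so their ratio carries over only if positivity is similar in research and CHW-only responses.
- No between-arm test of the percentage is specified, and reactions per course given is an ordinary tolerability measure.

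These points limit the concern without removing it. The narrow wording appears in four places, including the consent schedule and the only day-3 questionnaire in the appendix list (the contents of the CHW registers, Appendices 17 and 18, are not shown). Even under the broad wording, unvisited administrations stay in the denominator. A charter can set thresholds, but it cannot supply control-arm events that the protocol does not clearly require to be collected in the same way.

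**Conclusion.** The concern holds in limited form, as a should-fix. The stated formula divides by all administrations while the protocol is contradictory on who is checked. The understatement runs from none (everyone checked) to about 3.3-fold (research responses only). The upper end rests on using participants as a proxy for administrations, on reading the 9,000 as the research-response subset, and on no reactions being detected elsewhere.

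Separately, a comparable control-arm rate for the stopping-rule events is not clearly secured, because facility recording and the board's remit are worded around DHAP and the expected rates are undefined. This is a lack of clear specification; it does not show that control data will be absent or that the stopping rule must fail. Per-administration percentages should not be read as a comparison of the arms, because the treated populations differ.

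**What to change.** 1. Reconcile Sections 2.3, 2.4.2, 2.7 (Table 2), 2.8 (Secondary Aim 3), 3.1 and the label of Appendix 9 on whether CHW-only responses have a day-3 check. Which arrangement applies is for the sponsor to decide.
2. In Section 3.1, make administrations with a completed day-3 check the denominator for reactions found at that check. Report it by arm, together with the number of administrations not checked.
3. State that adverse and serious adverse events at facilities are recorded on the same form (Appendix 13) in both arms.
4. State in Section 3.2 what the expected control-group rates are: observed in this trial, or taken from a named outside source.
5. Give the monitoring board deaths and hospitalisations by arm, per resident of the response areas or per catchment person-time, so that the denominator does not depend on who was treated.

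The cost is a protocol wording change and some extra reporting work in control facilities. The form already exists, and no treatment, dose or sample size changes.

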#### Treatment notes

For this study, DHAP will be given in Eurartesim© tablets. While full product details are available from the manufacturers Sigma Tau (www.sigmatau.com), the following key issues are highlighted when administering DHAP, and summarised as a decision tree in Figure 5. DHAP is not recommended during the first trimester of pregnancy. Women of reproductive age (12-49) will be asked about their pregnancy status and if pregnant, the last time they felt the baby move. Any woman unsure of her pregnancy status will be offered a rapid pregnancy test, or referred to the nearest health facility. Women reporting that they are pregnant and have not felt the baby move (still in the first trimester), testing pregnant through the rapid pregnancy test or who are unsure of their pregnancy status will be tested with a malaria RDT and referred to the health center if testing positive. Pregnant women before the first trimester will not be treated with DHAP; pregnant women beyond the first trimester will be treated with DHAP. Additionally, DHAP should be administered with water no less than 3 hours after the last food intake, and no food should be taken within 3 hours after each dose. Any individual who does not wish to take, or cannot take DHAP, for whatever reason, will be offered the standard of care i.e. AL.

If a patient vomits within 30 minutes of taking DHAP, the whole dose will be re-administered. If a patient vomits within 30-60 minutes, half the dose will be re-administered. Re-dosing will not be attempted more than once. If the second dose is vomited, the patient will be referred to the nearest health centre. No more than two courses of DHAP will be given within a 12 month period, with a 2 month window between the two courses due to the long elimination half-life of piperaquine. Individuals identified during RFTAT responses who have been treated with DHAP in the previous 2 months, or twice within the previous year will be given AL.
[figure not shown]

Figure 5 - Decision tree for patient interactions during passive case detection at the health center/ health post and RFDA with DHAP in the community. mRDT, Malaria RDT; WRA, Women of Reproductive Age; HC, Health Center; DHAP, dihydroartemisinin-piperaquine. *due to previous dosing schedule.

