### Research Response

In order to assess parasite clearance and the risk of re-infection following a reactive response, a subset of index cases will be randomly selected for follow-up by a research team within each participating health center catchment area (Figure 7). Equal numbers of index cases will be randomly selected in each arm and in each clinic, with a minimum of two index cases per month in each arm i.e. minimum of four total per month. Only index cases reporting no history of travel will be enrolled. A questionnaire will be administered to all individuals participating in the reactive research responses and a finger prick blood sample will be obtained to collect dried blood spots (DBS) for study research purposes only. Participants will be adequately protected with risks minimized as much as possible during sample collection (see Section 3.1 for more information). Information collected through the questionnaire will include demographic information, current symptoms, recent malaria history, travel history, RDT result, HS RDT result (in RFDA arm only) and treatment administered (Appendix 6 and Appendix 7). Geocoordinates will be collected for each household targeted for a reactive response. Blood samples will be used to detect asexual stage parasites by PCR and all positive samples will be genotyped using a molecular bar code.

Follow-up visits will be conducted 3 (Appendix 9), 30 (Appendix 10) and 90 (Appendix 10) days after the initial reactive response. Additional information will be collected from each targeted individual on signs and symptoms of malaria, other treatments received, adherence to the drugs given (if any), and adverse reactions. A finger prick blood sample will be collected from each individual as a DBS at the 30 and 90 day follow-up visits. From the initial reactive response visit, blood samples will be used to detect asexual stage parasites by PCR and all positives genotyped using a molecular bar code.

For research responses enrolled in the RFDA arm, consenting individuals will be tested using the HS RDT as well as the standard RDT. No treatment decisions will be made based on the results from either the HS RDT or the standard RDT, rather they will all be offered DHAP. Individuals who do not consent to be enrolled in the RFDA arm will continue to receive the standard of care i.e. testing with a standard RDT and if positive, treatment given according to national policy.

[figure not shown]

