## Adequacy of protection against risks

We will administer an informed written consent and assent form in English or the local language as required by the participant. Table 4 outlines the exclusion criteria, inclusion ages and consent / assent forms that will be administered. For the household survey, written consent for participation in the survey and intervention will be provided by an individual who is at least 18 years of age according to the laws of Zambia. These forms will be read and explained or will be given to participants to read themselves and will include a full description of voluntary participation, the right to withdraw from the study at any time and the right to not answer any question. The forms will also address the risks, benefits and purpose of the intervention and study, including what we hope to learn. For individual’s ≥1 month and less than 18 years of age, consent will be sought from the head of household or parent/household guardian above age 18. For children greater than six years and less than 18, oral assent will be sought from the child. We will train all interviewers extensively on the consent and assent procedures. Checks in the field by the project team, including observation of a reactive response, assessment of completed consent statements and questioning of the interviewer will ensure the consent process is strictly followed. The confidentiality procedures (listed in section 2.11 on p33) are designed to meet all contingencies so that the privacy of the participants is preserved.

| **Study/intervention data collection** | **Exclusion** | **Inclusion Ages** | **Consent/Assent** |
| --- | --- | --- | --- |
| **Endline Survey** | < 1 month or >15 years of age | ≥1 month and <6 years old | Adult Consent (Appendix 3) |
|  |  | 6-<15 years old | Oral assent (Appendix 19) |
| **RFTAT intervention** | Severe malaria patients, First trimester pregnant women, < 1 month of age | ≥3 months old | DHAP Consent (Appendix 11) |
| **RFDA intervention** | Severe malaria patients, First trimester pregnant women, < 3 months of age, individuals contraindicated for DHAP | ≥3 months old  ≥1 month old | Oral Assent 6-17 years (Appendix 16) |
|  |  |  | Reactive research response (Appendix 8) |
| **Research around reactive responses for RFTAT and RFDA** | < 1 month of age | ≥1 month old | Oral Assent 6-17 years (Appendix 16 |
|  |  |  |  |

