- Before providing any woman of reproductive age (12-49) with DHAP we will first ask women if they are pregnant or potentially pregnant
- If a woman reports being pregnant, to determine the trimester of the pregnancy, in addition to asking how many months pregnant she may know she is, she will be asked about the date of her last menstruation and, if necessary, if quickening has occurred (i.e. if she has felt the baby move inside of her)
- To offer women that are unsure of their pregnancy status or who are potentially pregnant a rapid pregnancy test to confirm pregnancy or not
- To clearly explain to women the potential risk of taking DHAP during the first trimester of pregnancy and allow them to opt out of receiving DHAP while still receiving the standard of care in Zambia (the RFTAT intervention)

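### The protocol's text on DHAP in pregnancy is inconsistent: exclusion against opt-out, a withholding sentence that misses its group, two ways of setting trimester, and a rapid-test rule with no trimester condition

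*Protocol*

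**What the plan says.** Five places in the protocol bear on who is offered DHAP in pregnancy.

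- **Section 2.2.2.1, Treatment notes.** It opens with "DHAP is not recommended during the first trimester of pregnancy". Three kinds of women are to have an RDT and be referred if positive. The first two are "Women reporting that they are pregnant and have not felt the baby move (still in the first trimester), testing pregnant through the rapid pregnancy test"; the third is women unsure of their status. The next sentence is "Pregnant women before the first trimester will not be treated with DHAP; pregnant women beyond the first trimester will be treated with DHAP". The section also says that anyone who cannot take DHAP, whatever the reason, is offered the standard of care.
- **Section 3.1, Table 4, RFDA row.** The exclusions are "Severe malaria patients, First trimester pregnant women, < 3 months of age, individuals contraindicated for DHAP". The row for research responses excludes only infants under 1 month.
- **Section 3.1, list of measures on first-trimester risk.** Women aged 12-49 are asked about pregnancy before DHAP is given. To set the trimester, a pregnant woman is asked how many months along she is; in addition "she will be asked about the date of her last menstruation and, if necessary, if quickening has occurred". Women who are unsure are offered a rapid pregnancy test. The last bullet has staff explain the "potential risk of taking DHAP during the first trimester of pregnancy and allow them to opt out of receiving DHAP", with the standard of care kept for those who decline.
- **Section 2.4, Reactive responses.** In the RFDA arm, everyone living within 140 m of the index household is offered DHAP.
- **Section 2.4.1, Research Response.** In RFDA research responses, treatment is not to be decided by the results of "the HS RDT or the standard RDT, rather they will all be offered DHAP".

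**The concern.** The protocol treats first-trimester exposure to DHAP as a risk that needs a strategy, so the eligibility rule should read the same wherever a field worker looks it up. It does not. One place excludes, another offers an opt-out, and the sentence that should withhold treatment misdescribes its group. Trimester, on which all of this turns, is assessed in two ways.

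The Definitions of Key Terminology say that most responses are performed by a single community health worker, so often nobody else is present to settle the ambiguity. At stake is whether a given woman is dosed or withheld according to the section the team was trained on. A secondary effect is that RFDA coverage among women aged 12-49 could differ between teams for reasons unrelated to the design.

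**Working it through.** There is no plan figure to reproduce. The check is to trace four kinds of women through each section.

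| Woman | Section 2.2.2.1 | Section 3.1 | Section 2.4.1 read literally |
|---|---|---|---|
| (1) Known to be in the first trimester | DHAP not recommended; RDT, and referral if positive, when no movement is felt; not named in the withholding sentence | Table 4: excluded. Risk list: risk explained, may opt out; no bullet withholds DHAP | Offered DHAP |
| (2) Past the first trimester by dates, no movement felt | Classed as first trimester; RDT and referral route | Classed as beyond the first trimester by months or last menstruation | Offered DHAP |
| (3) Positive rapid pregnancy test, beyond the first trimester | RDT and referral route in one sentence; treated with DHAP in the next | Test offered; no action stated after a positive result | Offered DHAP |
| (4) First trimester, RDT positive, in an RFDA research response | Referred because of the RDT | Research row of Table 4 does not exclude her, so she can be enrolled and tested; RFDA row excludes her from DHAP | RDT drives no treatment decision; offered DHAP |

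**Case 1.** Table 4 and the opening of 2.2.2.1 agree with each other. The risk list does not repeat their rule, and the withholding sentence in 2.2.2.1 does not state it, because no woman is pregnant before the first trimester.

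**Case 2.** This is the firmest conflict. Knowing what the sponsor intends for first-trimester women does not settle it, because the two methods disagree on whether she is one. Once 3.1 classes her as beyond the first trimester, the last clause of "Pregnant women before the first trimester will not be treated with DHAP; pregnant women beyond the first trimester will be treated with DHAP" would treat her, while the preceding sentence of 2.2.2.1 sends her to RDT and referral.

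**Case 3.** The conflict lies between adjacent sentences of 2.2.2.1: the rapid-test route has no trimester condition, and the treatment sentence has one.

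**Case 4.** Section 2.4.1 has no cross-reference to the Table 4 exclusions, and its instruction about RDT results does not fit the RDT-based referral in 2.2.2.1. The wording in 2.4 also lacks a cross-reference. This is the lesser point.

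**Illustrative size.** Only the total of about 30,000 response participants comes from the protocol (Project summary). The assumptions are: half in the RFDA arm (15,000), women aged 12-49 making up 20-25% of them, 5-8% of those women pregnant, and one third of pregnancies in the first trimester.

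- Pregnant women: 15,000 × 0.20 × 0.05 = 150, to 15,000 × 0.25 × 0.08 = 300.
- First trimester: 150 / 3 = 50, to 300 / 3 = 100.
- Share of the arm: 50 / 15,000 = 0.3%, to 100 / 15,000 = 0.7%.

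For case 2, assume that the first trimester ends at week 13 and movement is first felt at 16-20 weeks. The two methods then disagree for 3 to 7 of 40 weeks, or 3 / 40 = 8% to 7 / 40 = 18% of gestation.

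**The case against.** The intent is clear enough to a fair reader. Section 2.2.2.1 says DHAP is not recommended in the first trimester and refers RDT-positive women, which agrees with Table 4. The withholding sentence contains an evident slip. The screening questions in the risk list would have little purpose unless they gated dosing, so the opt-out bullet may be an added safeguard for women of uncertain status. The rapid test is offered to women who are unsure, whose gestation is probably unknown, and routing them to referral withholds DHAP. In case 2 the stricter reading withholds DHAP from a woman past the first trimester, which is not first-trimester exposure. Section 2.4.1 is mainly about not acting on RDT results and can be read as subject to Table 4. Figure 5, which summarises the rules, is not shown.

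Much of this stands, and it limits what can be claimed. Three stronger readings are tempting and are not supported:

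- A reader might infer that RDT-positive people who cannot take DHAP are left without action. Section 2.2.2.1 offers them the standard of care and refers RDT-positive first-trimester women, and the risk list keeps the standard of care for women who opt out.
- A reader might infer that the protocol means to offer DHAP to first-trimester women by default. Table 4 and the opening of 2.2.2.1 say otherwise. The defect is that the risk list does not say so.
- A reader might infer that Figure 5 is wrong. It cannot be judged here.

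The objection does not remove the inconsistencies. An inferable intent is not a stated rule, an evident slip still has to be corrected, and intent does not choose between two methods of setting trimester. Section 3.1 indeed gives no dosing rule of its own, but its classification feeds the treatment clause in 2.2.2.1.

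**Conclusion.** The text is wrong as written and should be corrected before it is used for training. Four inconsistencies hold on the wording alone:

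1. Exclusion in Table 4 against opt-out in the risk list of the same section.
2. A withholding sentence that does not name the first trimester.
3. Two methods of assigning trimester that classify some women differently.
4. A rapid-test route with no trimester condition beside a sentence that has one.

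The offer-to-all wording in 2.4 and 2.4.1 is a lesser defect: a missing cross-reference and, in 2.4.1, a poor fit with RDT-based referral.

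The group is small. The 50-100 first-trimester women (0.3-0.7% of an assumed 15,000) and the 8-18% of gestation rest on assumed rates and are illustrative only. The conclusion does not depend on them. The sample size calculation is unaffected, and any effect on coverage would be slight. The weight comes from this being a safety eligibility rule applied mostly by lone workers.

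**What to change.** Reconcile section 2.2.2.1, sections 2.4 and 2.4.1, Table 4 and the risk list in 3.1 into one eligibility sequence, stated once and cross-referenced elsewhere. It should contain:

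- one statement on the first trimester that replaces both the withholding sentence in 2.2.2.1 and the opt-out bullet in 3.1;
- one stated method of assigning trimester, including what to do when the sources of information disagree;
- one stated action after a positive rapid pregnancy test;
- wording in 2.4 and 2.4.1 that makes the offer of DHAP subject to the DHAP exclusions, and that reconciles the instruction not to act on RDT results with the referral route in 2.2.2.1.

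Then check that Figure 5 and the DHAP consent sheet (Appendix 11) agree with the sequence. Which clinical rule applies is for the investigators and the safety board; the request is only that the passages state one rule.

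The cost is a protocol wording amendment, any matching change to the consent sheet or decision tree, and a refresher for field teams. No new procedure is needed, because the RDT and the pregnancy test are already planned.
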